### Study design

The study is designed to monitor a longitudinal oral health education program for Aboriginal children aged 6 months followed for 2 years. In order to assess the effect on dental caries, a sample size of 150 participants will provide at least 80 percent power at the two sided 95 percent level of significance to distinguish between a prevalence of 2 versus 1.6 ECC ( ECC includes decayed ,missing and filled primary teeth ) at 30 months allowing for as much as a 33% attrition rate (chosen following discussions with AHWs on population movement). The reference rate for ECC is informed by data provided by the Centre for Oral Health Strategy, New South Wales (personal communication and work by Jamieson et al
[6]). The forward projection is that the participating children will have a reduction in the mean ECC score of 20 percent, to 1.6. This is highly plausible and is based on previous trials. For example a recent study where fluoride toothpaste was posted to families living in low socio-economic areas of Northern England reported a 16 percent reduction in dental caries in young children
[32]. No personal advice was offered. An Australian study reported a 33 percent reduction in dental caries
[33,34], following a health education program which included the application of topical fluoride.

The rejection of the null hypothesis will be considered indicative of a clinically significant benefit, and would provide a strong case for proceeding to a Phase III evaluation.

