**Methods/Design:**

This is a Phase II single arm trial designed to gather information on the effectiveness of a dental health education program for Aboriginal children aged 6 months, followed over 2 years. The program will deliver advice from Aboriginal Health Workers on tooth brushing, diet and the use of fluoride toothpaste to Aboriginal families. Six waves of data collection will be conducted to enable estimates of change in parental knowledge and their views on the acceptability of the program. The Aboriginal Health Workers will also be interviewed to record their views on the acceptability and program feasibility. Clinical data on the child participants will be recorded when they are 30 months old and compared with a reference population of similar children when the study began. Latent variable modeling will be used to interpret the intervention effects on disease outcome.

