[27]. A study of Northern Territory Aboriginal communities reported that only 20 percent of children used toothpaste daily and most did not begin using toothpaste until the age of four
[28]. The AIHW reports that ‘Less than 5 percent of remote Aboriginal and Torres Strait Islander pre-school children brush their teeth on a regular basis
[6]. Causes identified for low use of toothbrushes and fluoride toothpastes include poor levels of carer education, high purchase costs and difficulties in establishing tooth brushing routines. The proposed program addresses these crucial barriers to the prevention of early childhood caries in Aboriginal families. AHWs will provide vulnerable families with advice on effective tooth brushing, use of fluoride toothpastes and support the development of these behaviours by the distribution of oral hygiene products and materials including toothbrushes, fluoride toothpaste and trainer cups
[29]. These preventive strategies are based on high quality evidence derived from large population based randomized controlled trials and systematic reviews
[30] and show a benefit when used over time. Therefore the theoretical construct underpinning the program is the tailoring of the oral health message to the specific oral health and psychosocial needs of Aboriginal families and their children
[31].

The dental health education program and the research instruments have been piloted with Aboriginal families, Aboriginal Health Workers and aligns with the Aboriginal Health and Medical Research Council policies on partnerships with Aboriginal Communities.

The primary endpoint for the study will be:

The prevalence of ECC at the age of 30 months. These data will be compared with similar children aged 30 months participating in the Aboriginal communities in the first year of the program implementation.

The secondary endpoints include:

Changes in the oral health knowledge of the primary care giver over time.

Early referral for dental care, if the oral health screening by the Aboriginal health workers notes a problem.

Impact of the child’s oral health on the family.

Acceptability of the program recorded by interviewing parents and AHWs at the end of the program.

Sustainability assessed by interviewing managers of the participating Aboriginal Community Care Health Services.

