### Data collection

Information on baseline and subsequent visits (Figure
1) will be collected by the AHWs utilizing a structured questionnaire which has been piloted in an Aboriginal community.

The key topics for intervention are:

Bottle use, when and what to put in it.

Tooth brushing – using the tooth brush

Toothpaste - using the toothpaste, how much to put on the brush and safe storage

Dietary habits – reported changes in the consumption of sugary snacks and drinks

AHWs screen for caries
[35] – positive/negative

Reported dental problems

At the final 30-month assessment the carers will be asked about their perceptions of the feasibility, and acceptability of the program. In addition selected questions from the Dental Discomfort Scale
[36] and the Being a Mother Scale
[37] will be included in the assessment. The Aboriginal Health Workers and the senior management team at each AMS will be interviewed to record their views on the facilitators and barriers to the wider implementation of the program. All interviews will be recorded, transcribed and analyzed for recurrent themes.

The end of trial dental assessment will be undertaken by a calibrated examiner using the same diagnostic criteria when collecting the dental caries data on the historical reference group.

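### The stated 80% power holds only for a test against a fixed value of 2, not for the comparison with examined reference children named under the primary endpoint

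*Protocol article*

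**What the plan says.** The Study design section gives the sample size: "a sample size of 150 participants will provide at least 80 percent power". The test level is worded as "at the two sided 95 percent level of significance", the target difference is given as "to distinguish between a prevalence of 2 versus 1.6 ECC", and losses are covered by "allowing for as much as a 33% attrition rate". The 2 and 1.6 are mean counts of decayed, missing and filled teeth, since the same section projects "a reduction in the mean ECC score of 20 percent, to 1.6". It says that the reference rate is informed by outside data from a state oral health body and by published work. Only program participants are counted.

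The Statistical analysis section agrees with this. It evaluates the 30-month result against a null hypothesis that sets the rate at 2, in a trial described as single arm.

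Three other places describe a different comparison. Under the primary endpoint in Methods/Design: "These data will be compared with similar children aged 30 months", drawn from the communities in the first year of the program. In the Abstract, the children's data are to be "compared with a reference population of similar children when the study began". In Data collection, a calibrated examiner will work "using the same diagnostic criteria when collecting the dental caries data on the historical reference group".

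**The concern.** A power calculation belongs to one test. The one given here treats the 2 as a constant. If the primary result is instead set against a group of examined children, the comparator is an estimate, its variance adds to that of the program group, and the same 100 program children give less power.

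The Study design section makes rejection of the null the case for going on to Phase III. If the analysis follows the comparison named under the primary endpoint, a non-significant result could be read as evidence against the program when the comparison had little chance of detecting the target. If it follows the fixed null, the interval leaves out whatever uncertainty there is about the true level in similar children.

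**Working it through.** **Inputs from the article.** Enrolled 150; attrition 33%, so 150 × 0.67 ≈ 100 evaluable; means 2.0 and 1.6 (difference 0.4); two-sided 5%, which is how the stated significance level is read.

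**Assumed, because not given.** Variance equal to the mean (Poisson), chosen because it comes close to the article's own sample size. The number of reference children, nR, is varied.

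**Step 1: the stated figure, as a test against a fixed 2.**
- Null variance throughout: Φ(0.4/√(2/100) − 1.96) = Φ(2.828 − 1.960) = 80.7%.
- Null variance for the test, alternative variance for the power: Φ((0.4 − 1.96 × √(2/100))/√(1.6/100)) = 83.4%.
- Exact Poisson: 83.9%.
- Other variants at n = 100 lie between 80.6% and 88.5%.
- In reverse: n = 2 × (1.960 + 0.8416)²/0.4² = 98.1, rounded up to 99; 99/0.67 = 147.8, so 148 enrolled against the stated 150.

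The stated power is therefore reproduced for the fixed-value test.

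**Step 2: the same difference against sampled reference children.** SE = √(1.6/100 + 2/nR); power = Φ(0.4/SE − 1.96).

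| Reference children | SE | Power |
|---|---|---|
| 50 | 0.237 | 39% |
| 100 | 0.190 | 56% |
| 200 | 0.161 | 70% |
| 400 | 0.145 | 79% |
| 1,000 | 0.134 | 85% |

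For 80%: nR = 2/((0.4/2.8016)² − 1.6/100) = 456.1, so 457 reference children.

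**Step 3: the same loss in other terms, at 100 versus 100.**
- Detectable difference at 80% power: d = 2.802 × √((4 − d)/100) gives d ≈ 0.52 teeth, a reduction of about 26% rather than 20%.
- 95% half-width: 1.96 × 0.190 = 0.37 teeth for the difference, against 1.96 × √(1.6/100) = 0.25 for the one-sample mean.
- If all 216 families in the Recruitment section enrol, 216 × 0.67 ≈ 145 are evaluable. Against 145 reference children, SE = √(3.6/145) = 0.158 and power is 72%.

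**Step 4: sensitivity to the SD.** With an SD of 2 in both groups, power at 100 versus 100 falls to 29%, and the fixed-value test falls to 52%. The fixed-value test drops below 80% once the SD exceeds 0.4 × 10/2.8016 = 1.43, just above the Poisson value of √2 = 1.41. Methods/Design cites a fivefold higher risk of further lesions in a child who already has one, which points towards overdispersion but gives no SD.

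**The case against.** The strongest reply is that the article is consistent where it matters. The power sentence and the primary analysis both use a fixed 2, the trial is single arm, and the arithmetic can be reproduced. No passage specifies a two-sample test. The reference group might also be large: the Abstract speaks of a reference population, and the outside data behind the 2 are of unknown size. A condensed article may leave the size of that group to the full protocol.

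Much of this stands. A reader might infer that the 80% is a miscalculation, that the trial's true power is 56%, or that a real 20% reduction would be missed about as often as it is found. The documents support none of these. For the fixed null the figure is right under Poisson variance. The 56% depends on 100 reference children and Poisson variance, neither of which is stated. The only null that the article gives for the Phase III decision is the value 2. The missing group size alone would also be no finding.

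What the reply does not remove is the conflict within the article. The comparison written directly under the primary endpoint, and repeated in the Abstract, is with similar children. Data collection shows that caries data are gathered on a reference group. A power figure printed for one test does not carry over to the other unless the reference group is several times the size of the evaluable program group, and nothing in the article indicates that it is.

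**Conclusion.** The point holds as a mismatch between the stated power and the stated primary comparison, not as an arithmetic error. At least 80% is correct for the one-sample test against 2, given Poisson variance and 100 evaluable children. For the comparison with examined reference children, power depends on a number that the article does not give: about 39% to 79% for 50 to 400 reference children, and 80% only from about 457. All these values assume Poisson variance and would be lower with overdispersed counts. Which power applies cannot be settled until the article says which comparison is primary.

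**What to change.** Reconcile the primary endpoint text in Methods/Design with the Statistical analysis section, so that one primary comparison is named, and bring the Abstract, Study design and Data collection into line.

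- **If the reference children are the comparator:** state their planned number and the variance assumed. Restate the power, or the detectable reduction, for the two-group comparison. Base the primary test and interval on the standard error of the difference.
- **If the fixed value of 2 is kept:** say that the 80% applies only to that test, state the variance assumed, and describe the comparison with reference children as secondary, with its lower power stated.

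The cost is a rewritten sample-size paragraph and a less favourable stated power. If the two-group comparison is primary, the interval is also wider (at 100 versus 100, a half-width of about 0.37 rather than 0.25 teeth). No extra program families are needed.

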### Recruitment

Aboriginal Health Workers know their communities well, and which families are most in need of support. AHWs from six Aboriginal Medical Services (AMS) will each recruit 12 families with a child six months of age. Up to three AHWs per Aboriginal Medical service will work on the project giving a potential sample of 216. The recruitment strategies have been successfully piloted and AHWs were able to recruit 6 families within a week, so the suggested figure of 12 families per AHW for the main study is certainly reasonable. The AHWs will explain the project to parents/carers and be responsible for obtaining a signed consent form from participating families.

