After extensive consultation with a number of Aboriginal Controlled Community Health Service staff and the Director of the National Aboriginal Health College a promising family focused dental health education program has been developed. It will be delivered by Aboriginal Health Workers (AHSs) inviting Mothers with young children to an appropriate local ACCHS clinic to offer diet advice, ensure fluoride toothpaste is used on a regular basis and to screen children for early signs of early childhood caries. A home visit will be undertaken if families find it difficult to attend, miss an appointment or the AHW thinks a home visit is the best way to maintain contact with the family.

This is an innovative approach which responds to the severely limited availability of dental personnel within Aboriginal communities, the very early onset of the disease in Aboriginal children, and recognizes the importance of AHWs to local communities. Early childhood caries develops at a time when contact with dental personnel is very limited in comparison to the regular contact young families have with Aboriginal Health Workers. In addition the active recruitment to the program by trusted local AHWs will overcome the problem that individuals from deprived backgrounds are less likely to consent to targeted preventive intervention schemes
[8,9].

The training program for AHSWs to explain how to implement the program has been tested and the supporting information leaflets have been piloted in collaboration with Aboriginal families. Both evaluations were positive in terms of their appropriateness and potential sustainability. The pilot data have been used to develop the protocol for a Phase II evaluation which will determine whether there is sufficient promise to warrant the investment in a large scale confirmatory Phase III cluster randomized trial. The development and evaluation of a program to improve oral health deliverable by community health personnel is relevant not only to Aboriginal communities, but also to other groups with limited access to dental services, including rural and remote communities throughout Australia.

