### Statistical analysis

The primary analysis will be an evaluation of the estimated prevalence of caries at 30 months in relation to the null hypothesis that the rate is 2. Descriptive analyses of other endpoints will be applied using methods appropriate for continuous and categorical data. Estimates will be presented with two-sided 95 percent confidence intervals.

The qualitative data from the interviews will be analyzed , using the ‘framework’ method
[38]. The qualitative data will be fractured and examined for key topic areas. The data will then be systematically coded according to the topic areas and thematic charts (in spreadsheet form) will be constructed. Summaries of the relevant parts of transcripts will be written into the charts so that each case may be examined across a range of different and emerging themes
[38].

The proposed study is rare in health promotion research in that it is not a ‘before and after’ design but is longitudinal, building information and capacity over time
[39]. The longitudinal design helps the investigative team to test for mediation effects in a more rigorous manner than cross sectional designs
[40]. For example the multi-wave nature of the assessments delivers the following methodological advances:

i. prevention on the reliance of retrospective reports of health behavior from mothers (removal of memory biases);

ii. reliable baseline latent variables of fluoride use and oral health (reducing bias of measurement error);

iii. enable the testing of growth models and unbiased parameter estimation of the fluoride intervention using resampling methods (bootstrapping). This third improvement would be made possible by controlling for concurrent baseline disease levels. Cole and Maxwell
[39] suggest that Structural Equation Modelling (SEM) will greatly assist in testing the direct and indirect effects of a longitudinal intervention. Crucial is the development of a model which can reduce bias frequently inherent in two wave designs. These are sometimes referred to as ‘half-longitudinal’
[41]. The proposed design therefore has innovative features not utilized in previous caries prevention programs which will enable true longitudinal investigation benefiting from the latest developments in statistical modeling.

One potential model which could be assessed utilizing Structural Equation Modeling is shown in Figure

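### The 80% power claimed for 150 children makes no allowance for clustering by service and health worker, and does not survive modest clustering

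*Protocol article*

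**What the plan says.** The sample-size statement (Study design) is that "a sample size of 150 participants will provide at least 80 percent power", two-sided, "to distinguish between a prevalence of 2 versus 1.6 ECC", after losing up to 33% of participants. The same section describes the effect as a mean: "the participating children will have a reduction in the mean ECC score of 20 percent, to 1.6". Attrition is the only allowance made.

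The Recruitment section sets out the structure: "AHWs from six Aboriginal Medical Services (AMS) will each recruit 12 families with a child six months of age". There are up to three workers per service, giving a potential sample of 216. These workers also obtain consent, and the Methods/Design section has them deliver the program.

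The Statistical analysis section tests the 30-month result against a fixed null rate of 2 and adds: "Estimates will be presented with two-sided 95 percent confidence intervals". It names no variance method. The Background section says that the study will judge whether there is "sufficient promise to warrant the investment in a large scale confirmatory Phase III cluster randomized trial".

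**The concern.** Children in one service share a community and a clinic, and children under one worker share the person who recruited, advised and screened them. If their caries outcomes are positively correlated for these reasons, 100 children carry less information than 100 independent children, and a calculation that allows for attrition alone overstates power.

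The protocol treats rejection of the null as a strong case for going on to Phase III, so the operating characteristics of this one test matter. A test that accounts for clustering at 150 children may miss a real 20% reduction more often than the stated power implies. A test that does not account for it would give a false go signal more often than 5% of the time.

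**Working it through.** **Inputs from the protocol.** N = 150, two-sided alpha 0.05, power at least 80%, means 2 and 1.6, attrition 33% (Study design); one-sample comparison with a fixed rate of 2 (Statistical analysis); six services, up to 3 × 6 = 18 workers, 12 families per worker, 18 × 12 = 216 (Recruitment).

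**Assumptions.** The variance equals the mean (Poisson), because no standard deviation is stated. ICC is 0.01 to 0.10, because none is given. Cluster sizes are equal.

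**Step 1: reproduce the stated power.** Evaluable children: 150 × 0.67 ≈ 100.
- Score form: power = Φ[(0.4 − 1.96√(2/100)) / √(1.6/100)] = Φ(0.1228/0.1265) = Φ(0.971) = 83.4%.
- Null-variance form: power = Φ[0.4/√(2/100) − 1.96] = 80.7%. This form needs (1.96 + 0.84)² × 2/0.16 ≈ 98.1 evaluable children, and 98.1/0.67 ≈ 147 enrolled.

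So 150 fits a calculation with independent children plus attrition.

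**Step 2: room left for clustering.** The score form needs 92.0 evaluable children for 80% power, so the largest tolerable design effect is 100/92.0 = 1.09. For the null-variance form it is 100/98.1 = 1.02.

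**Step 3: power with clustering at N = 150.** Design effect DE = 1 + (m − 1) × ICC; the effective sample size 100/DE goes into the score form.
- By service, m = 100/6 = 16.7.
- By worker, m = 12 × 0.67 ≈ 8, which corresponds to about 12 or 13 workers for 150 families.

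| ICC | DE, service | Power | Type I error if clustering is ignored | DE, worker | Power |
|---|---|---|---|---|---|
| 0.01 | 1.16 | 77% | 6.8% | 1.07 | 81% |
| 0.02 | 1.31 | 71% | 8.7% | 1.14 | 78% |
| 0.05 | 1.78 | 57% | 14.2% | 1.35 | 70% |
| 0.10 | 2.57 | 41% | 22.1% | 1.70 | 59% |

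The type I error column is 2Φ(−1.96/√DE). Correct intervals would be √DE times as wide as unadjusted ones: 7.5% wider at a service ICC of 0.01 and 60% wider at 0.10. In the score form, power crosses 80% at a service ICC of 0.087/15.7 ≈ 0.006 or a worker ICC of 0.087/7 ≈ 0.012.

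**Step 4: the potential 216.** 216 × 0.67 ≈ 145 evaluable, m = 24.1 per service. Power by service is 89% at ICC 0.01, 83% at 0.02, about 80% at 0.025, 66% at 0.05 and 46% at 0.10.

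**Step 5: six services as the unit of inference.** With a t reference on 5 degrees of freedom (critical value 2.57) and noncentrality 0.4/√(1.6 × DE/100), power at 150 is about 72% at ICC 0 and about 60% at ICC 0.02.

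**The case against.** The best defence is that this is a condensed article and that the choice of standard error is commonly left to an analysis plan, which is not shown. That stands for the intervals. A reader might infer that the planned intervals treat children as independent and are therefore too narrow, but the Statistical analysis section names no variance method, so the type I error figures apply only if clustering is ignored. The defence does not cover the power statement, which is made in this document and tied to 150.

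Other parts of the defence also stand:
- No ICC is given, so the large losses at 0.10 illustrate one end of an assumed range. At a worker ICC of 0.01, power stays at about 81% in the score form.
- The stated power does not require a design effect of exactly 1; it survives to about 1.02-1.09.
- Recruiting towards 216 would absorb a modest service ICC.
- The primary endpoint is also described as a comparison with similar children in the participating communities. If those children came from the same services and were compared within service, shared service differences would largely cancel. The service-level figures apply to the comparison with a fixed rate of 2.

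Three further inferences should be resisted. The planned cluster randomized Phase III does not show that the protocol accepts that outcomes cluster, since no reason for that design is given and it may be chosen for delivery or contamination. The protocol does not say that the six services differ in diet or access. And the study need not end without an ICC, because service and worker follow from the recruitment structure and the ICC can be estimated afterwards.

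**Conclusion.** The point holds for power. At 150 children the stated 80% has almost no room for clustering, although the design has children recruited and treated by up to 18 workers in six services. Any positive ICC lowers the true power: to about 77% to 41% for service ICCs of 0.01 to 0.10, and to about 81% to 59% for worker ICCs over the same range. How much is lost cannot be settled from the protocol.

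For the analysis, the conclusion is conditional: if the test against 2 is run without allowing for clustering and the service ICC is 0.01 to 0.10, intervals will be too narrow and the two-sided type I error will be about 7% to 22%.

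All figures rest on Poisson variance and equal cluster sizes. Counts more variable than Poisson would lower power further. This should be corrected, but it does not undermine the study as a Phase II evaluation.

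**What to change.** - **Study design:** restate the power at 150, and at 216, under a stated range of design effects, giving the standard deviation and ICCs assumed.
- **Statistical analysis:** specify that the primary estimate against the null of 2 uses standard errors that allow for clustering by service and health worker, with a small-sample correction because there are only six services.
- **Planning output:** report the service and worker ICCs with confidence intervals as input to the cluster randomized Phase III, noting that six services will give an imprecise estimate.

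The cost is a somewhat less favourable stated power and wider intervals. No new data are needed, provided that each child's service and worker are kept in the dataset.
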